#### Cost-effectiveness and cost-utility

An economic evaluation is conducted alongside the randomized trial and is performed according to the intention-to-treat principle. We will evaluate the relationship between costs and health outcomes of treatments. We will perform both a cost-effectiveness analysis with PTSD symptoms as effect measure and a cost-utility analysis using QALYs.

*EuroQol (EQ-5D-5L):* The EQ-5D-5L is a self-report instrument comprising five dimensions (mobility, self-care, daily activities, pain/discomfort, and depression/anxiety), that is administered at T0 and all follow-up measures to calculate health utilities [66]. Health utilities will be calculated from the EQ-5D-5L scores by using the Dutch tariff to obtain preference-based utilities [67].

*Trimbos/iMTA Questionnaire for costs associated with Psychiatric illness (TiC-P):* The TiC-P is used to measure healthcare uptake and productivity losses (absenteeism and presenteeism) between baseline and last follow-up measure (T3). Healthcare costs per participant will be determined by multiplying healthcare uptake by unit costs as described in the Dutch costing guideline [68].

#### Measurement - other study parameters

*International Trauma Questionnaire (ITQ, part 2):* The Internationale Trauma Vragenlijst (ITV) is the Dutch translation of the International Trauma Questionnaire (ITQ). It is a self-report questionnaire that measures PTSD and complex PTSD (CPTSD) and is based on the International Classification of Disease (ICD-11), in which (in contrary to the DSM-5) the diagnosis complex PTSD is also included. Part 1 of the questionnaire consists of 9 questions involving PTSD and part 2 consists of 9 questions regarding CPTSD, scored on a Likert scale ranging from 0 to 4 with higher scores indicating higher levels of complaints [69]. In this study, only part 2 is assessed.

*Childhood trauma Questionnaire – short form (CTQ-sf):* The CTQ-sf is a 28-item self-report questionnaire with questions on a Likert scale ranging from 1 to 5, that measures child abuse and neglect and can be used to identify individuals with a history of maltreatment. It has good validity and reliability and is the most widely used instrument to assess childhood trauma [70, 71].

*Daily Emotional Support (DES) subscale from Social Support Questionnaire of Transactions (SSQT):* The DES subscale of the SSQT consists of 5-items and is included in the current study to measure emotional support [72].

*Neurocognitive assessment:* Impulsivity and cognitive interference are measured by a computerized emotional STROOP task including substance-related, PTSD-related, and neutral words (Inquisit) and delay discounting is measured using a computerized version (MATLAB) [73]. Neurocognitive measures of impulsivity, like delay discounting, and cognitive/attentional interference (such as the STROOP task) have been found to relate to a higher chance of treatment dropout and earlier relapse, in several substance use disorders [74–76]. We therefore included a delay discounting task and an (emotional) STROOP task in this study, as in SUD/PTSD patients, these neurocognitive measures may influence treatment response and/or relapse.

*Baseline characteristics:* Demographic characteristics, treatment history, and patient preference of type and timing of PTSD treatment are administered.

*Treatment characteristics:* The number of sessions of PTSD-treatment attended and the number of sessions of SUD-treatment attended are administered.

*Therapist characteristics:* Therapist working experience and therapist preference of type and timing of PTSD treatment are administered.

### Data analyses

All analyses will be conducted on an intention-to-treat basis. To compare types and timing of PTSD treatment, (Generalized) Linear Mixed Models ((G)LMMs) will be used to model the primary and secondary outcome measures, with the underlying distribution (e.g., normal, gamma, (negative) binomial) depending on the type of outcome variable and its distribution. Next to these analyses based on classical statistics, a (hierarchical) Bayesian approach will be used to model the outcome parameters so that the relative evidence for the null-hypothesis (no differential effects) and the alternative hypothesis can be estimated. Prior distributions have been specified.

#### Primary outcome measure

The primary outcome measure will be the continuous variable PTSD symptom severity, as measured with the CAPS-5 at all follow-up assessments. Additionally, based on the same CAPS-5 assessments we will evaluate the dichotomous variables loss of PTSD diagnosis (no longer meeting criteria for PTSD) and full remission of PTSD (CAPS-5 score < 20), as these dichotomous variables are easy to interpret and are needed to calculate the number needed to treat. Most secondary outcome measures are continuous variables, with the exception of treatment completion of PTSD treatment and completion of SUD treatment, which are dichotomous variables.

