### Participants

Participants are recruited at the Jellinek Center in Amsterdam and Utrecht. Study participants are patients who apply for SUD treatment at the addiction treatment center, for whom treatment of co-occurring PTSD is also indicated. All patients treated in the two participating locations are adults (18 years of age or older), and both males and females can participate in the study. The criteria for inclusion in the study are a) age 18 years or older; b) SUD(s) according to the DSM-5 (American Psychiatric Association, 2013), with a primary diagnosis involving one of the following substances: alcohol, cannabis, cocaine (snorting), amphetamine, benzodiazepine, opioid; c) PTSD according to the DSM-5 criteria; d) sufficient understanding of the Dutch language to be able to fill out Dutch questionnaires and follow therapy in Dutch. The exclusion criteria are: a) acute psychotic disorder; b) mental retardation or cognitive impairment (estimated IQ < 70); c) current physical or sexual abuse or death threats; d) current acute suicidal behavior (high suicide risk and suicide attempt in the last 3 months); e) life threatening self-injury; f) homelessness; g) involvement in a compensation case or legal procedures concerning admission or stay in the Netherlands, h) involvement in legal procedures regarding the index trauma, i) engagement in any other current PTSD treatment.

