### Procedure

#### Recruitment

All patients attending an intake at the Jellinek Center are screened for PTSD with the J-PTSD screening questionnaire [30]. After the intake, the intramural or extramural SUD treatment is planned according to regular procedures and usually starts between 1 to 3 months after the intake. Patients with a positive PTSD screener are invited for further assessment with the Clinician Administered PTSD Scale for DSM 5 (CAPS-5) interview, also a regular procedure that is already implemented at the Jellinek Center. If the patient meets the criteria for PTSD, the psychologist informs the patient about the study and hands over the patient information letter. The psychologist asks consent of the patient for being contacted by telephone by a researcher to receive more information about the study. Potential participants receive written and oral information about the study and are invited for an informed consent procedure and screening of in- and exclusion criteria. Eligible patients are invited for the baseline (T0) assessment. Written informed consent is obtained prior to the assessment. All reasons of potential participants to decline participation in the study will be monitored.

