#### Primary outcome measure

The main study parameter is severity of PTSD symptoms and is measured at every assessment with the Dutch translation of the Clinician Administered PTSD Scale for DSM 5 (CAPS-5). The CAPS is the gold standard in PTSD assessment. It is a 30-item structured interview, corresponding to the DSM-5 diagnosis for PTSD, to assess PTSD symptoms over the past month. The sum of items 1 through 20 provides the total severity score [50]. The Dutch translation of the CAPS-5 has a high internal consistency for the full PTSD scale and a high interrater reliability score for the PTSD symptom severity score. Internal consistency for the symptom clusters is found to be acceptable [51]. All junior researchers were trained in the use of the CAPS-5 before conducting assessments and receive ongoing supervision throughout the study. Randomly selected CAPS-5 assessments are recorded on audio and scored by other researchers to check the interrater-reliability.

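### Full remission is defined by a CAPS-5 total below 20 alone, so a patient who still meets PTSD criteria at that visit can be counted as fully remitted

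*Protocol article*

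**What the plan says.** The Data analyses section of the protocol article (Primary outcome measure) makes continuous CAPS-5 severity the primary outcome. From the same interviews it adds two dichotomous variables: "loss of PTSD diagnosis (no longer meeting criteria for PTSD") and "full remission of PTSD (CAPS-5 score < 20"). It justifies them partly by ease of interpretation and partly because they "are needed to calculate the number needed to treat".

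The instrument description (Instruments, Primary outcome measure) states how the total is formed: "The sum of items 1 through 20 provides the total severity score". It gives neither the item range nor the severity at which an item counts as a symptom.

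Entry requires "c) PTSD according to the DSM-5 criteria" (Participants), with no minimum CAPS-5 total. No section makes loss of diagnosis a condition of full remission.

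**The concern.** A diagnosis depends on which symptoms are present. A total depends on how the item scores add up. The two classifications can disagree unless the diagnostic criteria force the total to 20 or more, and the article does not show that they do.

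If they disagree, one patient at one visit can be counted as fully remitted and also as not having lost the diagnosis. The label then claims more than the rule delivers. A number needed to treat built on it would count some patients who still have the disorder as successes. The two outcomes would also not be nested, although a reader would expect full remission to be the stricter one.

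**Working it through.** The cut-off of 20 is a definition, so there is no computed figure to reproduce. The check is whether the diagnosis and a total below 20 can coexist.

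**Inputs from the article.** Full remission is a total below 20 with no second condition. The total is the sum of items 1 to 20. Loss of diagnosis is a separate variable.

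**Assumptions, not in the article.** The diagnosis needs k symptoms. A symptom counts when its item scores at least t. Items are scored in whole numbers and can be zero. The base case is k = 6; k is varied from 4 to 8 and t from 1 to 4.

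**Lowest total compatible with the diagnosis.** This is k × t: each required symptom exactly at threshold and every other item at zero.

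| k | t = 1 | t = 2 | t = 3 | t = 4 |
|---|---|---|---|---|
| 4 | 4 | 8 | 12 | 16 |
| 5 | 5 | 10 | 15 | 20 |
| 6 | 6 | 12 | 18 | 24 |
| 7 | 7 | 14 | 21 | 28 |
| 8 | 8 | 16 | 24 | 32 |

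The overlap exists wherever the entry is below 20. At t = 1 or 2 it exists for every k from 4 to 8 (lowest totals 4 to 16). At t = 3 it exists up to k = 6 and closes from k = 7. At t = 4 it exists only for k = 4. In the base case it is open at 6, 12 and 18, and closed at 24.

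**Width of the overlap for k = 6.** The largest total that still counts as remitted is 19. The points left for any extra severity on the six symptoms and for the other 20 − 6 = 14 items are:

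- t = 1: 19 − 6 = 13
- t = 2: 19 − 12 = 7
- t = 3: 19 − 18 = 1

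For t = 2 the patient must have a total between 12 and 19 and still meet criteria. That is possible but narrow.

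**Effect on the number needed to treat.** Let d1 and d0 be the shares in two compared arms who are below 20 but still diagnosed. The stated rule gives a risk difference larger than that of the conjoint rule by d1 − d0. If the shares are equal, the number needed to treat does not change and only the absolute rates are too high, by d1 and d0. If they differ, it can move either way. The article gives neither share.

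**Sample size.** The Sample size section rests on pre-post change with effect sizes f = 0.15 and 0.10, not on a binary outcome, so nothing there changes.

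**The case against.** The strongest reply has three parts. First, the arithmetic uses a symptom count and a threshold that the article does not state, and it takes the extreme case of the minimum symptoms, each at threshold. It shows that the overlap is possible, not how often it occurs. Second, these are additional outcomes: the primary outcome is continuous and adjusted for baseline CAPS-5. Third, loss of diagnosis comes from the same interviews, so a number needed to treat free of this problem is available. All three stand, and they limit the weight of the point. They do not remove it, because the rule is stated in full and the overlap is present over most of the range shown.

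A reader might go further and infer that anyone below 20 at baseline counts as fully remitted. The article does not support that: the outcome is scored at follow-up, so such a patient counts only if the total is also below 20 then. It is true that no change from baseline is required. However, a state-based outcome in all randomised patients is a legitimate choice, and randomisation balances low-baseline patients in expectation.

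Nor does the article show a long gap between the diagnostic interview and T0. SUD treatment "usually starts between 1 to 3 months after the intake", but that interval starts at intake. The CAPS-5 interview follows intake and T0 precedes SUD treatment by 1 to 2 weeks, so the gap is shorter, and its length is not stated.

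The share below 20 at T0 is also unknown. Normal distributions with assumed means of 38, 35 and 32 and SDs of 9, 10 and 10 put 2.0%, 6.1% and 10.6% below 19.5, but the article gives no baseline distribution. Even if a share q counted as remitted in both arms regardless of treatment, the risk difference would shrink only by the factor 1 − q. With assumed remission of 20% versus 40%, the number needed to treat would go from 1/0.20 = 5.0 to 1/0.196 = 5.1 (q = 2%), 1/0.19 = 5.3 (5%) or 1/0.18 = 5.6 (10%).

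**Conclusion.** The point holds in a narrow form. Full remission is fixed as a score alone, and under plausible scoring rules a patient who still meets PTSD criteria can satisfy it. This rests on the assumed symptom count and item threshold: with six symptoms it holds at thresholds 1 to 3 and fails at 4.

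The frequency cannot be derived from the article and, given the narrow overlap, is probably small. What is affected is the meaning of the label, the absolute remission rates and, if the overlap differs between arms, the number needed to treat. The primary outcome, sample size and power are untouched.

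A reader might also infer that full remission could be reported more often than loss of diagnosis. That would need more patients below 20 who are still diagnosed than patients at 20 or above who are no longer diagnosed, and nothing in the article suggests it.

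Severity is minor; the change is a cheap improvement.

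**What to change.** Define full remission as a CAPS-5 total below 20 and no longer meeting DSM-5 PTSD criteria, both at the same assessment. It then becomes a subset of loss of diagnosis by construction.

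Keep all randomised patients in the main binary analysis and the number needed to treat, in line with the intention-to-treat rule in Data analyses. A figure limited to patients who met criteria and scored 20 or more at T0 is at most an optional sensitivity analysis. As a main analysis it would depart from that rule.

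The cost is one sentence in the outcome definition and a derivation from CAPS-5 data already collected. The downside is a slightly lower remission rate. The sentence should be fixed before the data are analysed, so that the choice is not made after seeing results.

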##### Objective 1: comparison separate PTSD treatments with SUD treatment only condition at 3-month follow-up

The 3 treatment conditions will be compared with SUD treatment only condition (PE vs SUD; EMDR vs SUD; ImRs vs SUD) at 3-month follow-up (T1 measure) with a linear regression model. Baseline CAPS-5 score will be included as covariate.

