## Methods

### Design

This study is a single blind 6-arm randomized controlled trial, consisting of 3 arms for simultaneous SUD/PTSD treatment with the PTSD treatments consisting of PE, EMDR, and ImRs, and 3 arms for sequential SUD/PTSD treatment with the PTSD treatments also consisting of PE, EMDR, and ImRs. Within the first 3 months after baseline, the three sequential treatment arms together form the SUD treatment only condition, as is depicted in the trial flow (Fig. 1). First, patients are randomly allocated to simultaneous PE, EMDR, or ImRs, or the SUD treatment only group. Subsequently, patients in this last group are randomly allocated to sequential PE, EMDR, or ImRs. The study is conducted at two departments of Jellinek. Jellinek is a Dutch addiction treatment facility center, offering both intramural and extramural addiction treatment. The duration of the study is planned to be 3.5 years, from inclusion of the first participant until the last follow-up measure of the final participant. The research protocol has been approved by the Medical Ethical Committee of the Amsterdam Academic Medical Centre (AMC) and the trial has been pre-registered at the Netherlands Trial Register (NTR L7885). The study is currently running.

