### Treatments

#### Treatment procedure

All participants receive regular SUD treatment plus either one of the following PTSD interventions: PE, EMDR or ImRs. SUD treatment starts directly after randomization for all participants. For patients allocated to the simultaneous treatment condition, PTSD treatment starts within 2 weeks after the start of the SUD treatment. For those in the sequential treatment condition, PTSD treatment starts 3 months after the start of the SUD treatment.

All PTSD treatments are provided by trained therapists and consist of twelve 90-min face-to-face sessions, conducted twice a week. Every treatment is executed by two different PTSD therapists, who alternately provide a session, inspired by the therapist rotation model. Among other things, this approach has shown to decrease avoidance behavior in sessions. Therefore, it is promising to improve trauma-focused treatment [37]. In all PTSD treatments, the focus of the first session is to present the treatment rationale and to list the traumatic experiences that will be addressed during the course of treatment. This overview is discussed and approved in peer-supervision after the first session. Henceforth the second session, each session contains 60 min of the specific intervention; EMDR, ImRs of PE. The rest of the session will be used to administer self-report questionnaires, to rehearse the rationale, to determine the specific trauma that will be addressed in the session and evaluation of the session. The self-report questionnaires are used to monitor symptom change during treatment. Although therapists encourage patients to be abstinent, this is not a requirement for the PTSD treatment. However, when a therapists notices a patients is intoxicated to such an extent that he/she has no capability to learn, the session is rescheduled.

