#### Therapists and training

Therapists in this study are experienced and licensed master’s level psychologists. All therapists are trained in all three methods to avoid therapist effects. Before participation in the trial, therapists attended a two-day training in PE provided by [name], a 5 day training in EMDR provided by [name] and a two-day training in ImRs provided by [name]. After finishing the trainings, all therapists had to pass a treatment integrity assessment with pilot patients by handing in a video for each type of therapy to demonstrate their competence. During the study, all therapists receive weekly one-hour peer-supervision sessions and tree yearly two-hour supervision sessions: one with each of the abovementioned trainers. There are several highly experienced therapists in each peer-supervision group. When questions arise that cannot be solved in peer-supervision, the trainers are consulted.

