#### Randomization and procedure

After the baseline assessment (T0), patients are randomly assigned to PE, EMDR, ImRs or SUD treatment only (each 25% chance). All patients receive SUD treatment shortly after the baseline assessment. Patients allocated to PE, EMDR or ImRs receive PTSD and SUD treatment simultaneously (75% of the sample), whereas patients in the 3-month SUD treatment only condition receive PTSD treatment after completing 3 months SUD treatment (25% of the sample). Patients in the SUD treatment only condition are randomly allocated to either PE (33% chance), EMDR (33% chance) or ImRs (33% chance) and start with the PTSD treatment after the 3 months follow-up assessment (T1).

After randomization, only disclosure of the timing will be given to the participants. Disclosure of treatment type will be done by the therapist at the start of the first session of the PTSD treatment.

Randomization is carried out by an independent researcher from Arkin who uses a computer-generated block randomization schedule. First patients are allocated to: simultaneous PE, simultaneous EMDR, simultaneous ImRs of sequential treatment with allocation probabilities per condition of 1/4. Block sizes are 4 and 8. Second, participants randomized to sequential treatment are allocated to: sequential PE, sequential EMDR or sequential ImRs, with allocation probabilities per condition of 1/3, after completion of the 3-months follow-up (T1) assessment. Block sizes are 3 and 6. Randomization is stratified by type of care (inpatient, daytreatment or outpatient) and location (Amsterdam or Utrecht). To prevent selection bias, all researchers are blind to order of block size and will not have access to the randomization schedule.

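### The Objective 1 regression makes no allowance for PTSD-therapist clustering, which exists only in the simultaneous arms up to T1; its standard errors may be understated if therapists differ in outcome

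*Protocol article*

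**What the plan says.** The Objective 1 section of the Protocol article sets three contrasts ("PE vs SUD; EMDR vs SUD; ImRs vs SUD"), analysed "at 3-month follow-up (T1 measure) with a linear regression model. Baseline CAPS-5 score will be included as covariate". No therapist term or clustered standard error is mentioned.

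The comparator is defined under Design: during the first three months "the three sequential treatment arms together form the SUD treatment only condition". Treatment procedure confirms that it has no PTSD treatment in that period: "For those in the sequential treatment condition, PTSD treatment starts 3 months after the start of the SUD treatment".

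On delivery, Treatment procedure states: "Every treatment is executed by two different PTSD therapists, who alternately provide a session". The only stated measure against therapist effects is under Therapists and training: "All therapists are trained in all three methods to avoid therapist effects".

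For Objectives 2 and 3 the article names mixed models with a random intercept and no therapist effect. The Bayesian companion analysis is called hierarchical, but its levels are not given.

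**The concern.** Patients are randomised individually, but those in the simultaneous PE, EMDR and ImRs arms share a pool of PTSD therapists. If some therapists get better results than others, outcomes of patients who share a therapist are correlated. A regression with condition and baseline CAPS-5 alone does not see that correlation.

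Cross-training is a sound answer for Objective 3. Every therapist can serve every treatment type, so a good or poor therapist moves both sides of a head-to-head contrast. In Objective 1 one side has no PTSD therapist, so nothing cancels. Alternating two therapists does not remove the problem either, because each arm mean still averages over the same pool.

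Objective 1 asks whether adding PTSD treatment helps at all. Its three contrasts draw on the same therapists, so an unusually strong or weak pool shifts all three in the same direction.

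**Working it through.** **Inputs from the article.** Sample size section: f = 0.15, Bonferroni alpha 0.0167, power 0.85, within-person correlation 0.60, 54 per arm, 20% dropout, 204 in total. Randomization section: allocation of 25% to each of four groups.

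**Stated figures.** The article gives no power for Objective 1. Its head-to-head figure reproduces: for a two-group, two-time-point interaction, lambda = N f² m/(1 − rho) = 108 × 0.0225 × 2/0.40 = 12.15, which gives power 0.852 at alpha 0.0167. Then 3 × 54 = 162, and 162/0.8 = 202.5, so 203; the stated 204 divides by four.

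**Size of an Objective 1 group.** 204/4 = 51 randomised; 51 × 0.8 = 40.8, about n = 41 analysed.

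**Assumed, because the article does not state them.** T is the number of PTSD therapists. ρ is the variance share of a single therapist, as a fraction of the variance left after baseline adjustment. Each treated patient has two therapists with weights 1/2 and 1/2, so the therapist variance per patient is ρ/2, while the arm mean carries about ρ/T.

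- True variance of arm minus control: (1 − ρ)/n + ρ/T + 1/n
- Variance the regression assumes: (1 − ρ/2)/n + 1/n
- True SE/reported SE = square root of the ratio, R
- True two-sided error at nominal 5% = 2[1 − Φ(1.96/R)]

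Worked case, T = 6 and ρ = 0.10: true = 0.02195 + 0.01667 + 0.02439 = 0.06301; assumed = 1.95/41 = 0.04756; R = √1.325 = 1.151; error = 2[1 − Φ(1.703)] = 8.9%.

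| T | ρ | R | True error |
|---|---|---|---|
| any | 0 | 1.000 | 5.0% |
| 6 | 0.02 | 1.031 | 5.7% |
| 6 | 0.05 | 1.077 | 6.9% |
| 6 | 0.10 | 1.151 | 8.9% |
| 10 | 0.02 | 1.018 | 5.4% |
| 10 | 0.05 | 1.045 | 6.1% |
| 10 | 0.10 | 1.088 | 7.2% |
| 20 | 0.05 | 1.019 | 5.5% |
| 20 | 0.10 | 1.039 | 5.9% |
| 30 | 0.10 | 1.022 | 5.5% |

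**Simulation of the stated regression** (four groups of 41, correlation 0.60 with baseline, two random therapists per treated patient).

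- With a correlation of 0.05 between patients sharing both therapists, which corresponds to ρ = 0.10, the error was 9.8%, 8.1%, 7.1% and 6.5% with 6, 8, 12 and 20 therapists. This is slightly above the formula.
- In the same runs PE versus EMDR stayed at 4 to 5%, as expected when therapists are crossed with treatment.
- The chance that all three Objective 1 tests are falsely significant together rose from about 0.3% without a therapist effect to between 1% and 2% with 6 to 8 therapists.
- The definition of the share matters. If it is taken of the total outcome variance, before baseline adjustment, 8 therapists give 5.6%, 7.5% and 9.6% at shares of 0.02, 0.05 and 0.10.

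**Offset from the stratification factors.** Randomisation is stratified by type of care and location, and the stated model includes neither. Omitting prognostic strata makes the reported SE too large. With ρ = 0.05 and 8 therapists, the simulated error was 6.6%, 6.0%, 4.8% and 4.9% when strata explain 0, 5, 10 and 15% of residual variance. At ρ = 0.10, with strata explaining 10%, it was 8.1%, 6.5%, 6.0% and 4.9% with 6, 8, 12 and 20 therapists. These strata shares are also assumptions.

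**The case against.** A reader might infer that the Objective 1 standard errors are too small as a matter of fact. The article does not support that. It needs therapists who differ in outcome and a modest number of them, and neither figure is given. The unadjusted strata push the other way, so even the net direction is not fixed. This part of the objection stands.

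Further points on the other side:

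- All patients receive SUD treatment from shared staff and programmes, so clustering is not confined to the treated arms. That is true, but SUD staff serve both sides and their effects largely cancel; the PTSD-therapist effect does not.
- If PTSD treatment had no effect whoever delivered it, there would be no treated-only therapist variance and the regression would hold its level. The inflation concerns inference to a wider population of therapists. Treating therapists as random is therefore a choice, though a natural one for a treatment meant for wider use.
- The Methodological considerations section presents cross-training as a guard against bias. It does not claim to protect the Objective 1 standard errors. Read that way it is correct, but the wording under Therapists and training is general.
- A condensed article may leave such detail to the full plan, and robust errors or a therapist level in the Bayesian model would be compatible with the text. However, the article does name a specific model for Objective 1 and says that therapist effects are avoided. The point is about the fit of that stated choice, not about a missing detail.

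**Conclusion.** The point holds in conditional form. Objective 1 is partially nested, the stated model does not allow for it, and the one stated safeguard works only between PTSD treatments. These three facts come from the text and need no assumed number.

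The size does rest on assumptions. For a single-therapist share of 0 to 0.10 and 6 to 20 or more therapists, the true SE is about 1.00 to 1.15 times the reported one and the true error about 5 to 9%. Simulation reaches nearly 10% at the unfavourable end. With many therapists or a share near 0.02 the effect is negligible, and prognostic strata left out of the model could cancel it. An accidental offset of unknown size is not a reason to keep the model.

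**What to change.** In the Objective 1 analysis, keep condition and baseline CAPS-5 and make these changes:

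- Add a therapist random effect that applies only to patients in the simultaneous PE, EMDR and ImRs arms and is zero for SUD only. Weight each patient's two therapists 1/2 and 1/2, or by sessions given.
- Use small-sample degrees of freedom (Satterthwaite or Kenward-Roger).
- Include type of care and location as covariates.
- If the therapist variance cannot be estimated stably, report the plain regression and the therapist-adjusted result side by side.

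Under Therapists and training, limit the statement about therapist effects to comparisons between PTSD treatment types.

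In simulation the treated-only therapist effect brought the error to about 4 to 6%. Separate residual variances by group are not needed.

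The cost is small: changed analysis wording and therapist identity for each session, which the article does not say is recorded but which should be known from treatment delivery. No extra patients or procedures are needed. The downside is confidence intervals about 2 to 5% wider when therapists do not in fact differ, and an imprecise therapist variance if there are few of them.
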